### National Coordination from Monitoring Center

Every six months a researcher from FCV will visit each center to evaluate the fulfillment of the protocol and the accomplishment of the Good Clinical Practice.

### Data base depuration phase

After completing all the data entry to the CRF the results will be audited and the detected errors evaluated and corrected. The information will be entered in two different databases by two different people and the records compared to detect any discrepancy using a statistical software (Epi-Info 6.04). The mistakes will be corrected according to the CRF, and the corrections registered.

Each patient will be identified using an internal code. All the photographs will be processed using a digital edition software.

### Statistical analysis

For the statistical analysis, Stata 8.0 will be used. The descriptive analysis will be composed of medians and proportions according to the nature of the variables, with their respective 95% confidence intervals. As a dispersion measurement the standard deviation will be calculated. The distribution of the variables will be studied using the Shapiro-Wilk test and the homocedasticity of the variances with the Levene test. To detect any difference between the groups, a T-test or a Mann Whitney test will be performed according to the distribution of the variables. The categorical variables will be compared using the Chi^2 ^test or the exact Fisher's test. If required, a model of multiple logistic regressions or a covariance analysis will be realized. Two interim analyses will be performed when 35 and 70% of the total sample is collected to determine differences in effectiveness and safety between the groups.

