### Sample size

The sample was calculated according to the arccosine formula considering a power of 80% and a type I error of 0.05. Assigning a successful rate of 30% in the control group and 60% in the active group, 95 participants will be needed. After adjusting for a loss rate of 5%, the total number of patients that must be recruited is 100 (50 patients per group).

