### Inclusion criteria

1. Men and women 18 years or older.

2. Capacity of attending the visits at the research site.

3. Confirmed diagnosis of DM type 1 or 2 according to the guidelines from the American Diabetes Association (ADA).

4. Presence of 1 or more DFU, less than 15 cm in its biggest diameter, with a Texas University score ≤ 2.

5. Pharmacological treatment for glycemic control.

6. Willingness to participate in the study and to sign the informed consent form.

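### The adjusted analysis is optional with no stated trigger; one main analysis, adjusted for baseline ulcer size, should be named in advance

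*Protocol article*

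**What the plan says.** All references are to the protocol article.

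- **Statistical analysis, continuous outcomes.** After Shapiro-Wilk and Levene tests, "a T-test or a Mann Whitney test will be performed according to the distribution of the variables". Categorical outcomes get a chi-square or Fisher test. None of these uses a covariate.
- **Statistical analysis, adjustment.** "If required, a model of multiple logistic regressions or a covariance analysis will be realized". The text does not say what would make adjustment required, or whether the adjusted or the unadjusted result would then be the main one.
- **Endpoints.** The first item is the percentage reduction of the ulcer. Healing as a yes/no outcome is not listed.
- **Sample size.** The calculation is on a binary scale: "Assigning a successful rate of 30% in the control group and 60% in the active group, 95 participants will be needed".
- **Baseline size.** An eligible ulcer is "less than 15 cm in its biggest diameter", with no lower limit. Table 1 and the Initial visit section have ulcers measured at day 0.
- **Prognosis and allocation.** The Background names lesion severity among the things that affect healing. The Logistic phase section describes randomisation in blocks and mentions no stratification by ulcer size.

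**The concern.** An adjusted model that may or may not be run, on a condition nobody has written down, leaves two candidate results for the same comparison. If the choice between them is made with the data in view, the nominal 5% error rate is no longer assured.

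The second issue is efficiency. Entry size can vary widely, the document itself treats lesion severity as relevant to healing, and the measurement is already taken before treatment starts. A default analysis without it may give up precision that costs nothing to use. With 50 patients per arm, that could matter.

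**Working it through.** **Inputs.** From Sample size: power 80%, type I error 0.05 (taken as two-sided, since sidedness is not stated), success 30% versus 60%, 95 patients before losses, 5% loss, 100 recruited in equal arms. Assumed, because the document does not give it: the correlation r between baseline size and the outcome as analysed.

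**1. The plan's own figure.** The arcsine effect is h = 2·asin(√0.6) − 2·asin(√0.3), and n per arm = 2(1.960 + 0.842)²/h².

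- Without continuity correction: 41.8 per arm, 84 in total.
- With continuity correction, n/4·(1 + √(1 + 4/(0.3n)))²: 48.2 per arm, 96.5 in total. This is within two patients of the stated 95.
- Losses: 95/0.95 = 100, as stated.

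The sample size is not in dispute here. The 95 is used below as the reference.

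**2. What adjustment could gain.** A linear covariance analysis multiplies the variance by 1 − r². Set the effect so that the unadjusted comparison of 47.5 per arm has 80% power: (1.960 + 0.842)·√(2/47.5) = 0.575 SD. Then power = Φ(2.802/√(1 − r²) − 1.960), and the number giving the same 80% power is 95·(1 − r²).

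| r (assumed) | Variance factor | Power at 95 | Patients for 80% power |
|---|---|---|---|
| 0 | 1.00 | 80.0% | 95 |
| 0.2 | 0.96 | 81.6% | about 91 |
| 0.3 | 0.91 | 83.6% | about 86 |
| 0.5 | 0.75 | 89.9% | about 71 |
| 0.7 | 0.51 | 97.5% | about 48 |

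**3. Type I error.** Simulation with no treatment effect: 50 per arm, 4,000 trials per setting (Monte Carlo standard error about 0.35 points), r = 0, 0.3 and 0.5. The outcome was either normal, or capped at 100 as min(100, 60 + 40 × latent value).

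| Rule | Normal outcome (r = 0 / 0.3 / 0.5) | Capped outcome (r = 0 / 0.3 / 0.5) |
|---|---|---|
| Shapiro-Wilk, then t or Mann-Whitney | 4.6 / 4.6 / 4.9% | 4.8 / 5.0 / 5.1% |
| Fixed covariance analysis on log baseline | 4.8 / 4.6 / 4.9% | 5.0 / 5.0 / 4.5% |
| Better of the two always reported | 5.2 / 6.0 / 7.3% | 6.0 / 6.7 / 7.1% |

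**4. Simulated power** (same settings, latent effect 0.57 SD).

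- Normal outcome: the pre-test rule gave 80.7% at r = 0.3 and 80.6% at r = 0.5; the fixed covariance analysis gave 84.2% and 90.2%.
- Capped outcome: 76.4% and 76.6%, against 79.2% and 86.0%.
- At r = 0 there was no gain: 80.2% against 80.6% (normal), 76.5% against 75.9% (capped).

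The cap is mild. It puts 1 − Φ(1) = 16% of control and 1 − Φ(0.43) = 33% of active patients at 100.

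**5. The pre-test when many ulcers heal.** If 30% and 60% of values are exactly 100, and the others are normal with mean 45 and SD 30 (assumed) and capped at 100, Shapiro-Wilk rejected normality in at least one arm in 2,000 of 2,000 simulated trials of 47 per arm. The rule then leads to Mann-Whitney.

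**The case against.** The case for leaving the text alone has real force.

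- **Validity.** An unadjusted comparison of randomised arms is valid. Adjustment improves efficiency; it does not correct an error. This stands.
- **Baseline is not ignored altogether.** A percentage reduction is already scaled to the patient's own starting size. Only the correlation left after that scaling yields a gain, and it may be small or nil. This stands, and it is why the range must start at r = 0.
- **Reach of the formula.** The factor 1 − r² belongs to linear covariance analysis. No gain was computed for a rank-based or a logistic model. In a logistic model the benefit is in power, not in a narrower interval for the odds ratio. This stands.
- **A condensed article.** Covariate lists and model details commonly sit in a fuller document. The absence of named covariates is therefore not held against the plan. The conditional rule is different: the article states it.
- **Worst case.** The 5.2–7.3% assumes that the more favourable result is reported every time. Nothing in the document says that this is intended.

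A reader might also infer that switching between t-test and Mann-Whitney offers several p-values, or that a t-test would be applied to data piled up at 100%. The document does not support either. A pre-stated switch yields one p-value, it held its error rate in step 3, and in step 5 it always led to Mann-Whitney. What the switch does leave open is which quantity is being compared.

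**Conclusion.** The point holds in a limited form. The plan makes adjustment conditional without a trigger, and the second result this allows can raise type I error to between 5% and a little over 7% if the more favourable one is always reported. A fixed covariance analysis stayed at 4.5–5.0%. Precision may also be lost: nothing at r = 0, and in the linear case a rise from 80% power to about 82%, 84% or 90% at r = 0.2, 0.3 or 0.5. The document gives no value of r, so the true gain is unknown.

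A reader might quote the gain as 10–33% more patients, from 1/(1 − r²) at r = 0.3 and 0.5 (1/0.91 = 1.10 and 1/0.75 = 1.33). That takes favourable correlations as given and leaves out zero, so it should not stand as the size of the problem. Nor do the documents show that the planned unadjusted test is wrong. The change is worth making because it closes an open choice at no cost, even if the precision gain proves to be nil.

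**What to change.** Delete the condition and name the main analysis before any comparison by arm is made:

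- **Ulcer reduction percentage (first endpoint).** Covariance analysis of the ranks of the percentage reduction on arm and log baseline ulcer size at day 0. Ranks are used because values pile up at 100% if many ulcers heal. The unadjusted Mann-Whitney test is supportive, and the normality and variance pre-tests no longer select the method.
- **If the 30% versus 60% success rate is the main outcome.** Use instead a logistic model on arm and log baseline size. Success would then need to appear among the endpoints. Which outcome scale is the main one has to be settled first.
- **Infection and adverse-event endpoints.** State one analysis for each. The planned chi-square or Fisher test can stay, provided no optional model is left beside it.
- **Several ulcers.** Patients may enter with more than one ulcer, so baseline size and percentage reduction should refer to the same ulcer or ulcers.

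The cost is analysis wording only. Day-0 ulcer size is already measured, and no visits, tests or patients are added.

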### Logistic phase

This phase will be managed by the physician in charge of the study and a professional nurse and will include the following activities.

1. Acquisition of the materials required for the development of the project.

2. Elaboration of flyers, promotional and educative material, procedures manual and Case Report Format (CRF).

4. Training of personnel that will participate in the study.

5. Treatment randomization

The treatment randomization will be realized by the epidemiologist of the Fundación Cardiovascular de Colombia (FCV). This randomization will be done in blocks in order to avoid long sequences of patients assigned to the same group and to reduce when possible, some of the bias inherent to the simple randomization process. Additionally, this randomization in blocks will facilitate the execution of interim analyses.

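### Effectiveness is compared at 35%, 70% and 100% of the sample, yet the article gives one type I error of 0.05 and no error control across looks; three unadjusted 0.05 tests would give about 10.6%, or 6–7% with Fisher's exact test

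*Protocol article*

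**What the plan says.** Three places in the protocol article bear on this point.

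- **Statistical analysis.** "Two interim analyses will be performed when 35 and 70% of the total sample is collected to determine differences in effectiveness and safety". The comparison is between the two arms. The section lists the tests (t-test or Mann-Whitney; chi-square "or the exact Fisher's test") and attaches no significance level to any look.
- **Sample size.** "The sample was calculated according to the arccosine formula", and the design values are given as "considering a power of 80% and a type I error of 0.05". The resulting number follows: "Assigning a successful rate of 30% in the control group and 60% in the active group, 95 participants will be needed". Allowing for 5% loss brings the total to 100, with 50 per group. The interim looks are not mentioned.
- **Logistic phase.** Block randomization is justified partly because "this randomization in blocks will facilitate the execution of interim analyses". The looks are therefore a deliberate design feature, but no boundary is given here either.

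The article does not say that each look is tested at 0.05, or what an interim result would trigger.

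**The concern.** The interim analyses compare the arms on effectiveness; they are not described as safety-only or blinded reviews. The article fixes their number, timing and purpose and quotes 0.05 as the type I error. It does not say how that 0.05 is shared among three looks. If the ordinary tests are simply applied each time, the stated 0.05 does not hold, and the chance of declaring an ineffective patch effective can roughly double.

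An early positive result would also be likely to exaggerate the effect. At the first look (17 and 18 patients, with a pooled rate near 50%), a difference must be about 1.96 × √[0.25 × (1/17 + 1/18)] = 0.33 to reach p < 0.05. That is larger than the 30-point difference for which the trial is sized.

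**Working it through.** **Inputs from the article.** Success rates 30% and 60%; power 80%; type I error 0.05; 95 evaluable and 100 recruited, 1:1; looks at fractions t = 0.35, 0.70 and 1.00. Sidedness is not stated; I take two-sided.

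**1. The plan's own sample size.**
- Arcsine effect: h = 2(arcsin√0.6 − arcsin√0.3) = 0.613.
- Per arm: n = 2(1.960 + 0.842)²/h² = 41.8, or 84 in total.
- With a continuity correction, (n/4)[1 + √(1 + 4/(n × 0.30))]² = 48.2 per arm, about 97 in total. This is close to the stated 95, though not exact.
- Loss: 95/(1 − 0.05) = 100, as stated.

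**2. Overall type I error with three unadjusted tests.** Under the null, the three z-statistics are jointly normal with correlation √(tᵢ/tⱼ): 0.707 (looks 1 and 2), 0.592 (1 and 3) and 0.837 (2 and 3). The probability that at least one |Z| exceeds 1.96 is 0.1059, or **10.6%**. With a one-sided 0.05 at each look, the result is 10.0%.

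**3. Check on binary data.** The same rule was applied with null success rates of 30%, 45% and 60%:

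| Patients per arm at each look | Uncorrected chi-square | Fisher's exact |
|---|---|---|
| 17/18, 35/35, 50/50 | 10.3–10.7% | 6.7–7.4% |
| 18/18, 35/35, 50/50 | 10.6–11.7% | 5.9–6.5% |
| 17/17, 33/33, 47/47 | 10.5–11.7% | 5.6–6.3% |

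Fisher's test is conservative at these sizes, which absorbs much of the inflation but not all of it.

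**4. Boundaries that restore 0.05.** An O'Brien-Fleming-type boundary sets |Z| > c/√t. Solving for an overall 0.05 gives c = 2.010:

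| Look | Critical \|Z\| | Nominal two-sided p |
|---|---|---|
| 35% | 2.010/√0.35 = 3.397 | 0.0007 |
| 70% | 2.010/√0.70 = 2.402 | 0.016 |
| 100% | 2.010 | 0.044 |

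A constant (Pocock-type) boundary needs |Z| > 2.284, or p < 0.0224, at each look. Using p < 0.001 at both interims and 0.05 at the end gives about 5.03% overall, marginally above 0.05.

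**5. Power for 30% against 60%** (arcsine, no continuity correction). The mean of the final z is 0.613 × √(N/4).

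| Evaluable N | Single test | O'Brien-Fleming | Pocock |
|---|---|---|---|
| 95 | 84.8% | 84.1% | 79.2% |
| 100 | 86.5% | 85.9% | 81.3% |

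**The case against.** A reader might infer that the trial's real type I error is 10.6%. The document does not support that. The figure needs 0.05 at every look and any crossing to count as success, and neither is written.

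This is also a condensed article. A boundary could sit in the full protocol or analysis plan, and its absence here does not show that none exists. Nor do the two statements strictly contradict each other, because an overall error of 0.05 with two interims is what a group-sequential design provides.

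A reader might further infer from the sample size that no adjustment was made. That does not follow either. The plain arcsine formula needs only 84, and 95 leaves more than 80% power under an O'Brien-Fleming rule. A continuity correction also comes close to 95, so the number settles nothing.

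Finally, the size of the inflation depends on the test, and Fisher's exact test is among those allowed.

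All of this stands, and it makes the point conditional. It does not remove it. The article commits to three effectiveness comparisons with ordinary tests and one quoted 0.05, and the two agree only if a boundary exists. Every test examined gives more than 5% without one. Fisher's test would not help with the first listed endpoint, percentage ulcer reduction: it is continuous, and an unadjusted t-test at the three looks gives about 10.8%.

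**Conclusion.** The point holds in conditional form. Effectiveness is to be compared three times, the sizing rests on a single-look formula at 0.05, and the article indicates no control of error across the looks. If each look uses an unadjusted two-sided 0.05 and any significant look counts as success, the overall type I error is about 10.6% by normal theory, about 10–12% for the uncorrected chi-square test and about 6–7% for Fisher's exact test.

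These figures assume one endpoint, looks at exactly 35%, 70% and 100% of the information, and 1:1 allocation. They show what the written plan permits; they are not the established error rate of the trial.

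**What to change.** State in the Statistical analysis section, before the first interim, a boundary that keeps the overall two-sided error at 0.05. If the full protocol already has one, cite it.

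- One suitable choice is O'Brien-Fleming-type nominal p of about 0.0007, 0.016 and 0.044 at 35%, 70% and 100%.
- A simpler choice is p < 0.001 at both interims and 0.05 at the end (overall about 5.03%).
- Other valid boundaries exist. A Pocock-type rule would take power at 95 evaluable patients just below 80%.
- Apply the boundary to one named effectiveness endpoint. The success rate used for sizing is not among those listed under Endpoints, so the text should say which comparison carries the 0.05.

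The cost is a few sentences. Early stopping for effectiveness becomes harder, and under O'Brien-Fleming the final threshold falls from 0.05 to about 0.044. Power at 95 evaluable patients falls by 0.7 percentage points (84.8% to 84.1%), so the sample size need not change.

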### Endpoints

At the end of the treatment the following endpoints will be evaluated:

1. Ulcer reduction percentage.

2. Complete cure of the infection that was present before the treatment.

3. Infection of the ulcers during the treatment.

4. Presence of adverse events related to the application of the patches.

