#### Specific Objectives

1. To evaluate the healing process of DFU using a NOP compared with placebo.

2. To assess the healing process of infected DFU using a NOP compared with placebo.

3. To identify adverse events associated with the application of NOP.

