### Follow-up visits

The treatment will last 90 days. During this period, the patients will be seen by the research group at least every two weeks until the healing of the ulcer or the end of the treatment. The frequency of the visits will vary depending on the clinical evolution of the patients. During each visit the healing process of the ulcer, the patient's health status and the presence of adverse events will be assessed. The patch will be applied and the evolution of the ulcers photographically registered. The maximum and minimum diameters of the ulcer will be measured using a graduated ruler and then registered in the CRF. The technique for the application of the patches, the identification of adverse events and the importance of reporting them, will be emphasized.

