### Evaluation and management of adverse events

During the visits the patients will be asked about adverse events. Each adverse event will be classified by the physician as serious or non-serious. A serious adverse event should meet one or more of the following criteria:

1. Death

2. Life-threatening

3. Hospitalization or prolongation of existing hospitalization

4. Persistent or significant disability/incapacity

The presence of a serious adverse event that puts the patient's life at risk and/or requires immediate medical or surgical procedure will call for the discontinuation of the treatment and the initiation of the pertinent medical management. The investigator will notify the Adverse Event Committee (AEC) of the FCV of any serious adverse event within 24 hours of learning about it.

A non-serious adverse event will be classified as follows:

1. Mild: The patient is aware of his/her symptoms and/or signs, but those are tolerable. Medical intervention or specific treatment is not required.

2. Moderate: The patients present troubles that interfere with his/her daily activities. Medical intervention or specific treatment is required.

3. Severe: The patient is unable to work or to attend his/her daily activities. Medical intervention or specific treatment is required.

The possible relationship between the adverse events and the tested medication will be classified by the investigator on the basis of his/her clinical judgment and the following definitions:

1. Definitely related: Event can be fully explained by the administration of the tested medication.

2. Probably related: Event is most likely to be explained by the administration of the tested medication rather than other medications or by the patient's clinical state.

3. Possibly related: Event may be explained by the administration of the tested medication or other medications or by the patient's clinical state.

4. Not related: Event is most likely to be explained by the patient's clinical state or by the use of other medications, rather than the tested one.

All the events will be reported to the AEC that, depending on its criteria, will decide the continuity of the patient in the study and therefore the breaking of the code. Although the project has been designed to minimize the inherent risks, any adverse event related to the study medication will be carefully evaluated by the AEC and the costs generated by the required treatment covered by the study.

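### The only adverse-event endpoint counts events judged patch-related, with no stated cut-off, so it can miss an unexpected harm and may be less sensitive than an all-event comparison by arm

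*Protocol article*

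**What the plan says.** All references are to the protocol article.

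- **Endpoints**, item 4: "Presence of adverse events related to the application of the patches". No other endpoint concerns adverse events in general. Item 3, infection of the ulcers during treatment, carries no relatedness condition.
- **Specific Objectives**, item 3: "To identify adverse events associated with the application of NOP". Objectives 1 and 2 name placebo as the comparator; this one does not.
- **Evaluation and management of adverse events**: "The possible relationship between the adverse events and the tested medication will be classified by the investigator on the basis of his/her clinical judgment". There are four grades: definitely, probably and possibly related, and not related. The last reads "Not related: Event is most likely to be explained by the patient's clinical state or by the use of other medications". The section does not say which grades make an event count towards endpoint 4.
- Collection is wider than the endpoint. **Follow-up visits** states "During each visit the healing process of the ulcer, the patient's health status and the presence of adverse events will be assessed", and the adverse-event section adds "All the events will be reported to the AEC" (the Adverse Event Committee).
- **Statistical analysis** plans two interim looks "to determine differences in effectiveness and safety between the groups", without naming the safety variable.

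**The concern.** Safety is half of the general objective. The trial has a placebo patch and blinding, so it can answer the causal question at group level: does one arm have more events than the other? Endpoint 4 puts an individual causal judgment in front of that comparison.

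The judgment is hard to make here. The investigator does not know whether a given patch releases nitric oxide. The Background states that topical donors have not been studied in human diabetic ulcers. The patients have diabetes and keep their other treatments apart from topical ones, so another explanation for an event will often be at hand. An unexpected effect of the patch, a systemic one for example, is the kind most easily classed as not related, and it would then leave the endpoint.

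The missing cut-off adds a second problem. Two analysts could count different events from the same case report forms, depending on whether they include the possibly related grade.

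**Working it through.** **No safety figure to reproduce.** The article states no adverse-event rate and no share of events expected to be judged related. The calculation below is an illustration on assumed values.

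**Inputs**
- 50 patients per arm and type I error 0.05 (Sample size section; sidedness is not stated, two-sided assumed).
- Assumed 90-day risk of any adverse event: 30% on placebo, 45% on active.
- Assumed share of events judged related: f.
- Simplification: each patient has at most one event.

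**Formula.** With n per arm, p̄ = (p₁+p₂)/2, SE₀ = √(2p̄(1−p̄)/n) and SE₁ = √((p₁(1−p₁)+p₂(1−p₂))/n):

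power = Φ((|p₂−p₁| − 1.96·SE₀)/SE₁)

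**All events counted.** p̄ = 0.375, SE₀ = √(0.375×0.625×0.04) = 0.0968, SE₁ = √((0.21+0.2475)/50) = 0.0957. Power = Φ((0.15−0.1898)/0.0957) = Φ(−0.416) = 0.34.

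**Case A: judgment cannot separate patch-caused from background events.** The same f applies in both arms, so both risks are multiplied by f.

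| f | Placebo | Active | Difference (points) | Power |
|---|---|---|---|---|
| 1.0 | 30% | 45% | 15 | 34% |
| 0.7 | 21% | 31.5% | 10.5 | 22% |
| 0.5 | 15% | 22.5% | 7.5 | 16% |
| 0.3 | 9% | 13.5% | 4.5 | 11% |

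The direction is the same at other assumed risks. For 10% vs 30%, power is 71% with all events, 56% at f = 0.75, 38% at f = 0.50 and 21% at f = 0.25.

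**Case B: judgment partly succeeds.** Background events (30 points in each arm) are called related with share b. Excess events (15 points, active arm only) are called related with share e. The filtered risks are 0.30b on placebo and 0.30b + 0.15e on active.

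| b | e | Placebo | Active | Power |
|---|---|---|---|---|
| 0.3 | 0.8 | 9% | 9% + 12% = 21% | 39% |
| 0.5 | 0.9 | 15% | 15% + 13.5% = 28.5% | 37% |
| 0.7 | 0.8 | 21% | 21% + 12% = 33% | 27% |

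The first two rows lie above the unfiltered 34%, the third below it.

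**Case C: an unrecognised harm.** If every excess event is classed as not related, e = 0. Both filtered risks equal 0.30b, and the endpoint shows no difference whatever the true excess.

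The effect of the filter therefore depends on how well blinded judgment identifies patch-caused events. The plan gives no information on this, and judgment is least reliable for a harm nobody expects.

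**The case against.** A reader might infer that the endpoint throws away the placebo comparison. The documents do not support that. Both arms wear patches, the endpoint wording is not confined to active ones, and relatedness is judged blind. The filtered endpoint is therefore still a valid randomised comparison. The interim analyses also plan a safety comparison between groups with no relatedness limit, and infection during treatment is a separate, unfiltered endpoint.

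The other side can add four points:

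- All events are recorded and reported, and an analysis plan that is not shown may add all-event tables. This stands as to the data. It does not change the endpoint, which is written and written restrictively. The interim plan names no safety variable, and reporting to the committee serves decisions on individual patients.
- If the three related grades all count, ambiguous events stay in, because possibly related covers events with more than one plausible explanation. That is a fair reading, but the article does not state it.
- The group does have human experience with this patch in cutaneous leishmaniasis, and the Background cites nitric oxide donors in healthy volunteers, so judgment has some basis. This stands, though neither population has diabetic ulcers.
- A filter that removes mostly background events can raise power. This stands (Case B), so loss of sensitivity is possible but not certain. Even the all-event comparison has only 34% power at the assumed risks.

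**Conclusion.** The point holds in a limited form. The one adverse-event endpoint rests on blinded investigator judgment with no stated cut-off. It can miss an unexpected harm attributed to the patient's condition or to other drugs, and it loses sensitivity when that judgment cannot tell patch-caused from background events. It does not invalidate the randomised comparison.

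At assumed risks of 30% vs 45% with 50 per arm, power goes from 34% to 11–22% if 30–70% of events are called related alike in both arms. It is 39% if 80% of excess and 30% of background events are called related. These figures rest entirely on assumed rates and assumed relatedness calls. What follows from the text alone is that a harm consistently classed as not related cannot appear in endpoint 4. The change is worth making because the data are already collected.

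**What to change.** Define endpoint 4 as two proportions: patients with any adverse event and patients with any serious adverse event. Compare each between randomised arms, with the difference and its 95% CI. Keep patch-related events as a secondary table, and state which of the four relatedness categories count in it.

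No new data are needed, since adverse events are documented at every visit and classified as serious or non-serious. The cost is a change of wording and one more table. The downside is that the headline count will include more background events that have nothing to do with the patch. The secondary table of related events keeps the narrower view available.
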